## Abstract

**Background:**

Type 1 diabetes is a main health burden with several related comorbidities. It has been shown that endothelial function, vascular structure, and metabolic parameters are considerably disrupted in patients with type 1 diabetes. Omega-3 as an adjuvant therapy may exert profitable effects on type 1 diabetes and its complications by improving inflammation, oxidative stress, immune responses, and metabolic status. Because no randomized clinical trial has examined the effects of omega-3 consumption in children and adolescents with type 1 diabetes; the present study aims to close this gap.

**Methods:**

This investigation is a randomized clinical trial, in which sixty adolescents with type 1 diabetes will be randomly assigned to receive either omega-3 (600 mg/day) or placebo capsules for 12 weeks. Evaluation of anthropometric parameters, flow-mediated dilation (FMD) as an endothelial function marker, carotid intima-media thickness (CIMT) as a vascular structure marker, proteinuria, biochemical factors including glycemic and lipid profile, blood urea nitrogen (BUN), creatinine, high-sensitivity C-reactive protein (hs-CRP), and erythrocyte sedimentation rate (ESR), as well as blood pressure will be done at the baseline and end of the trial. Also, dietary intake and physical activity will be assessed throughout the study. Statistical analysis will be performed using the SPSS software (Version 24), and *P* < 0.05 will be considered statistically meaningful.

**Discussion:**

It is hypothesized that omega-3 supplementation may be beneficial for the management of type 1 diabetes and its complications by reducing inflammation and oxidative stress and also modulating immune responses and glucose and lipid metabolism through various mechanisms. The present study aims to investigate any effect of omega-3 on patients with type 1 diabetes.

**Ethical aspects:**

This trial received approval from Medical Ethics Committee of Iran University of Medical Sciences, Tehran, Iran (IR.IUMS.REC.1400.070).

**Trial registration:**

Iranian Registry of Clinical Trials IRCT20210419051010N1. Registered on 29 April 2021

**Supplementary Information:**

The online version contains supplementary material available at 10.1186/s13063-021-05930-1.

## Background

Type 1 diabetes, a chronic disorder characterized by insulin deficiency, is generally thought to be precipitated by an immune-associated destruction of pancreatic β cells [1]. Genetic, environmental, and immunologic factors are involved in the pathogenesis of type 1 diabetes [2, 3]. In genetically susceptible subjects under the triggering impacts of environmental factors, autoimmune destruction of pancreatic β cells occurs, leading to insulin deficiency and, consequently, overt hyperglycemia. Polyuria, thirst, weight loss, and overt hyperglycemia are the most common symptoms of type 1 diabetes and diagnostic markers in adolescents [4, 5]. Compelling evidence indicates that there is a bidirectional correlation between the severity of type 1 diabetes and the probability of occurrence of its complications, including cardiovascular disorders, nephropathy, and neuropathy [6, 7]. Based on the results of a recent meta-analysis, the prevalence and incidence rate of type 1 diabetes were 9.5% and 15 per 100,000 people worldwide, respectively. The global rise in type 1 diabetes faces several challenges including the provision of insulin in underdeveloped and developing countries [8]. The lifetime economic burden of type 1 diabetes places a high disease cost on healthcare systems. Thus, developing novel therapeutic agents for the management of type 1 diabetes and its associated comorbidities is crucial [9].

Common approaches for the treatment of type 1 diabetes include administration of short, rapid, intermediate, or long-acting insulins, frequent monitoring of blood glucose, regular aerobic exercise, and dietary interventions such as having a healthy-eating plan, carbohydrate counting, and maintaining an ideal weight [10, 11]. Recently, researchers have become interested in exploring novel adjuvant therapies for the management of type 1 diabetes and its complications. Natural compounds possessing antidiabetic properties may be appropriate as adjuncts to existing therapies. Many new dietary supplements such as omega-3 may exert beneficial effects on type 1 diabetes and its related abnormalities, even equal to the effects of commonly known drugs [12]. Omega-3 polyunsaturated fatty acids including eicosapentaenoic acid and docosahexaenoic acid from seafood and alpha-linolenic acid from plant sources have several pharmacological properties, like antioxidant, anti-inflammatory, anti-tumor, anti-depressant, antihypertensive, and lipid-lowering effects [13]. They also enhance various types of metabolic disorders underlying the development of diabetes [14]. An in vivo study performed by Bi et al [15] demonstrated that omega-3 polyunsaturated fatty acids could potentially ameliorate type 1 diabetes and autoimmunity by decreasing serum concentrations of inflammatory biomarkers and modulating the differentiation of T helper and CD4^+^ T cells. Moreover, the results of an observational study by Norris et al. [16] exhibited that dietary intake of omega-3 fatty acids is correlated with declined risk of islet autoimmunity in children at elevated genetic risk of type 1 diabetes.

The present clinical study aims to assess the effects of omega-3 supplementation on endothelial function, vascular structure, and metabolic parameters in adolescents with type 1 diabetes. The primary objective of this research includes the assessment of flow-mediated dilation (FMD) as an endothelial function marker.

## Material and methods

### Study population

Adolescents with type 1 diabetes will be recruited from Mofid Children’s Hospital, Tehran, Iran, by an investigator. The investigator will conduct study assessments and screen study patients. The patients will be diagnosed by a specialist. It should be noted that because of the simultaneous occurrence of the coronavirus disease 2019 (COVID-19) pandemic and implementation of this study, researchers should expand their presence time in Mofid Children’s Hospital for achieving adequate participant enrollment to reach the target sample size. Patients that satisfy the inclusion criteria will be eligible to participate in this research. The inclusion criteria are considered as follows: adolescents aged between 10 to 18 years, whose body mass index (BMI) for age *Z*-score ranges between 5 and 85%, diagnosis of type 1 diabetes by a specialist, receiving insulin therapy, at least 5 years have passed since the diagnosis of type 1 diabetes, and a signed written informed consent form for participation in this trial. The exclusion criteria include subjects who are pregnant or breastfeeding, those affected by endocrine, metabolic, blood clotting, or any acute disorder, and patients who had diabetic ketoacidosis or hypoglycemia (blood sugar level lower than 50 mg/dl) in the last 12 or 3 months, respectively. In addition, subjects who consumed antihypertensive, anti-inflammatory, anticoagulant, lipid-lowering, and weight-lowering agents and antioxidant and omega-3 supplements in the last 6 months prior to the study will be excluded. Patients with fish or seafood allergies and smokers will also be excluded. Participants who are unwilling to continue collaborating on the trial or have poor compliance (less than 80%) with the assigned intervention will be withdrawn from follow-up.

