### Intervention

Sixty eligible adolescents with type 1 diabetes will be randomly assigned to the omega-3 (*n* = 30) and placebo groups (*n* = 30). Omega-3 capsules (600 mg) and identical placebo capsules will be respectively taken by patients in the intervention and control group once a day, for 12 weeks. The Karen Pharma & Food Supplement company will provide omega-3 capsules. Omega-3 and placebo capsules will be similar in weight, size, shape, taste, color, and odor. Placebo capsules will be also produced by Karen Pharma & Food Supplement company and contain 600 mg oral glycerin. Naringenin and placebo capsules will be given to the study patients for every one month in study visits. There are four study visits in our trial (before the intervention, after 1 month of intervention, after 2 months of intervention, and at the end of the intervention). Study patients will be informed how to use their supplements, and they will be weekly followed by phone calls. Compliance will be evaluated based on unused supplements by each person. The remaining capsules will be counted to determine total supplement intake. Furthermore, patients will be asked about any adverse events experienced following omega-3 consumption. If the reported adverse events are related to omega-3 consumption, participants will be asked to stop taking supplements, and they will be immediately referred to a specialist for therapy. It should be noted that there will be no dietary recommendation or dietary regimen for study patients.

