### Outcomes

The primary outcome of the current trial is the alteration in the value of FMD as an endothelial function marker at the end of the trial compared to the baseline value. Alterations in carotid intima-media thickness (CIMT), anthropometric indices including weight, height, and BMI for age *Z*-score, lipid profile including triglyceride (TG), high-density lipoprotein cholesterol (HDL-C), low-density lipoprotein cholesterol (LDL-C), and total cholesterol (TC), glycemic parameters including fasting blood sugar (FBS), hemoglobin A1C (HbA1C), fasting blood insulin (FBI), hemostatic model assessment of insulin resistance (HOMA-IR), and quantitative insulin sensitivity check index (QUICKI), plasma levels of high-sensitivity C-reactive protein (hs-CRP) and erythrocyte sedimentation rate (ESR), blood pressure, BUN, creatinine, proteinuria, energy intake, and consumption of nutrients are considered as secondary outcomes. Furthermore, at the beginning of the research, medical history and demographic factors including age, sex, race, education level, and marital status will be asked from all the patients or their legal guardians.

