### Data management and monitoring

A clinical trial monitor will occasionally supervise the study progress and ensure that patient rights and well-being are safeguarded. The clinical trial monitor will also supervise that the protocol, ethical requirements, standards, and regulations are being followed, the essential documentation is available, and collected data is accurately recorded. One of the researchers will check the coding, security, and storage of data. In addition, he/she will evaluate data entry and data values twice. If any participant reports the occurrence of adverse events, more information is required to make decision about excluding the participants from the trial. Unblinding is permissible in this situation based on the Medical Ethics Committee criteria [20].

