## Discussion

The role of omega-3 supplementation in the treatment and management of diabetes is still controversial. A recent preliminary trial investigating the effects of omega-3 in adults with type 1 diabetes demonstrated no significant changes in vascular health, glucose hemostasis, and metabolic parameters. However, limitations of the mentioned study including relatively small sample size, high number of subjects lost to follow-up, and the broad selection of people with different treatment regimens and duration of disease may cause bias in obtained results [21]. Another study performed by Casanova et al. [22] concluded that omega-3 supplementation improved arterial stiffness and endothelial function in hypertensive patients with high cardiovascular risk. Also, endothelial function was improved in endurance-trained athletes by a 3-week omega-3 supplementation [23].

Based on suspected mechanism of action of omega-3 reviewed in previous studies, we hypothesize that omega-3 may improve endothelial function, vascular structure, and metabolic parameters in adolescents with type 1 diabetes by attenuating the inflammatory response through suppression of the nuclear factor-kB (NF-kB) signaling pathway, reduction of oxidative stress via upregulating genes encoding cytoprotective antioxidant proteins such as heme oxygenase 1 (HO-1) and glutathione peroxidase (GPx), modulation of immune responses through decreasing adhesion molecule expression, adhesive interactions between leukocytes and endothelial cells, chemotactic response of leucocytes and T cell reactivity, and regulation of glucose and lipid metabolism by elevating fatty acid oxidation, decreasing the expression of sterol regulatory element binding protein-1c (SREBP-1c) and de novo lipogenesis, and preserving hepatic insulin sensitivity [24–28]. According to aforementioned hypothesize, the present trial is designed. Suggesting a natural compound as an option for the management and treatment of type 1 diabetes is one of the novel characteristics of the current clinical study. In addition, this research may lead to the cost-lowering effects due to the high burden and prevalence of diabetes in Iran and worldwide.

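### Hypoglycaemia and diabetic ketoacidosis are entry exclusions but not prespecified outcomes; after randomisation only a generic adverse-event question can capture them, and no comparison by arm is stated

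*Protocol article*

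**What the plan says.** All references are to the protocol article.

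- **Study population.** Candidates must be on insulin. Those excluded include "patients who had diabetic ketoacidosis or hypoglycemia (blood sugar level lower than 50 mg/dl) in the last 12 or 3 months, respectively". The section gives the two events no other role.
- **Outcomes.** "The primary outcome of the current trial is the alteration in the value of FMD as an endothelial function marker". The secondary list includes "glycemic parameters including fasting blood sugar (FBS), hemoglobin A1C (HbA1C), fasting blood insulin (FBI" and goes on to HOMA-IR and QUICKI, which makes five glycaemic measures. It closes with "blood pressure, BUN, creatinine, proteinuria, energy intake, and consumption of nutrients are considered as secondary outcomes". No hypoglycaemia, ketoacidosis or adverse-event item is in it.
- **Intervention.** "patients will be asked about any adverse events experienced following omega-3 consumption". There are four study visits, three of them after the start of treatment, and between visits "they will be weekly followed by phone calls". An event judged related to omega-3 leads to stopping the capsules and to referral.
- **Data management and monitoring.** "If any participant reports the occurrence of adverse events, more information is required to make decision about excluding the participants from the trial". Unblinding is allowed in that situation.
- **Statistical analysis.** Numerical and qualitative variables are compared between groups, as are changes in the outcome variables. Adverse events are not mentioned.
- **Discussion.** The hypothesis is improvement, including in metabolic parameters, through mechanisms such as "regulation of glucose and lipid metabolism by elevating fatty acid oxidation" and preserved hepatic insulin sensitivity.

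**The concern.** The plan hypothesises that the supplement acts on glucose metabolism in adolescents who all take insulin, and it measures the result by fasting glucose, HbA1c and three insulin-based measures at baseline and week 12. A mean can fall because high values come down or because low values become more frequent. Two measurements 12 weeks apart do not show episodes in between, so the listed outcomes cannot separate these explanations.

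The protocol already regards a glucose below 50 mg/dl and ketoacidosis as important enough to screen for, and it gives a threshold for the first. After randomisation neither is defined or prompted. The general question is phrased in terms of the supplement, and a participant or site may put a low reading down to insulin or to the disease. The stated uses of a report concern the individual: stopping, referral, exclusion, unblinding. At stake is whether the trial can show, beside its glycaemic results, how often these events occurred in each arm. An analysis plan written later cannot recover episodes that nobody asked about.

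**Working it through.** **1. What each section does with the two events**

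| Section | Hypoglycaemia / ketoacidosis |
|---|---|
| Study population | Both are exclusions; threshold of 50 mg/dl for the first, no definition of the second |
| Outcomes | Neither listed among 1 primary and 21 secondary items (blood pressure and nutrients counted as one item each) |
| Intervention | Not named; could fall under any adverse event |
| Data management and monitoring | Not named; a report leads to a decision on exclusion |
| Statistical analysis | Not named; no adverse-event comparison stated |

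The events can be recorded, but they are not prespecified, not prompted, and not assigned to a comparison.

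**2. The arm size**

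The Sample size calculation uses alpha 5% two-sided, power 90%, SD 2.7 in both arms and d = 2.5 for FMD:

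n = (1.960 + 1.282)² × (2.7² + 2.7²) / 2.5² = 24.5, rounded up to 25 per arm.

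This reproduces the stated 25. The stated 30 per arm is 25 × 1.2. Adding descriptive safety counts changes neither figure.

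**3. Contacts and exposure already planned**

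- Weekly calls: 60 × 12 = 720, if nobody drops out.
- Visits after the start of treatment: 60 × 3 = 180.
- Exposure: 60 × 84 / 365.25 = 13.8 patient-years.

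**4. What counts in 30 per arm could show**

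The article gives no event rate, so the 12-week risks below are assumptions shown as a range.

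*Zero events in one arm.* The exact two-sided 95% upper limit is 1 − 0.025^(1/n):
- n = 30: 11.6%
- n = 25: 13.7%

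*Chance of at least one affected participant in an arm of 30*, 1 − (1 − r)^30:
- r = 5%: 79%
- r = 10%: 96%
- r = 20%: over 99%

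The table would probably not be empty at these rates. This says nothing about telling the arms apart.

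*Power to detect a doubling*, 30 per arm, two-sided 5%, normal approximation with p̄ the mean of p1 and p2:

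Φ{ [ (p2 − p1) − 1.96 √(2p̄(1 − p̄)/30) ] / √[(p1(1 − p1) + p2(1 − p2))/30] }

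For 10% against 20%: (0.100 − 1.96 × 0.0922) / 0.0913 = −0.88, so power is 19%.

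| Assumed placebo share | Omega-3 share if doubled | Power |
|---|---|---|
| 5% | 10% | 11% |
| 10% | 20% | 19% |
| 20% | 40% | 39% |
| 30% | 60% | 65% |

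At a placebo share of 10%, the omega-3 share would have to reach about 41% for 80% power. The counts can describe; they cannot exclude a clinically relevant excess.

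**The case against.** The strongest reply is that the events are already covered. Patients are asked about any adverse event, they are called every week, and a ketoacidosis admission or a symptomatic low is an adverse event. Relatedness comes in only afterwards, when deciding about the capsules. This stands. A reader might infer that the events go uncounted after randomisation, or that sites would overlook them; the text supports neither. Nor does it show that placebo participants are not asked: the question is put to patients in general and the investigators are blinded. What remains is a vague question with no definition and no stated comparison.

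Second, this is a journal article. Prompted safety questions and tables by arm may be in the full protocol, the case report forms or an analysis plan. That is possible, and it makes this a recommendation and not proof of an error. Still, the article's outcome list is detailed, down to nutrient intake, and the article fixes how events are asked about and what a report is used for.

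Third, using an event as an exclusion does not oblige a trial to make it an outcome, and the article does not describe these events as the acute risks of its population. Both points are correct. The reason to count them is the combination of insulin-treated participants, a hypothesised effect on glucose metabolism and five glycaemic outcomes.

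Fourth, FMD is the sole primary outcome, so the main conclusion does not depend on this. That stands as well. A reader might also infer that the trial would go on to recommend the supplement. The article only hopes to provide supporting evidence and concedes that a longer treatment period might be needed.

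Finally, so small a trial cannot settle whether there is an excess. The figures above confirm this. It limits what the table can be used for, but it is no reason to leave the counts out.

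**Conclusion.** The point holds as a low-cost improvement. Hypoglycaemia and ketoacidosis are screened for at entry but are not prespecified outcomes. After randomisation they are captured, if at all, through an undefined adverse-event question, and the article states no comparison by arm, although five glycaemic measures are secondary outcomes with improvement hypothesised. FMD and its sample size are unaffected.

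The gain is modest: a defined count by arm to read beside HbA1c and fasting glucose. With 30 per arm, zero events would still leave an upper limit of 11.6%, and power for a doubling is 11% to 39% at assumed placebo shares of 5% to 20%. The conclusion rests on the article alone and assumes that no fuller document already prescribes these counts.

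**What to change.** 1. In Outcomes, add two descriptive safety outcomes: participants and episodes with blood sugar below 50 mg/dl, which is the protocol's own entry definition, and participants and episodes with diabetic ketoacidosis. The article does not define the latter, so the investigators should state the definition they use.
2. In Intervention, ask about both events by name, in both arms, at each planned weekly call and at each visit after the start of treatment. Record them whatever the judged relation to the capsule.
3. In Statistical analysis, report participants and episodes with confidence intervals by randomised arm, beside HbA1c and fasting glucose. Include episodes in participants who later stop or are excluded.
4. State that with 30 per arm these counts are descriptive and cannot exclude a clinically relevant excess. The table supports the reading of the glycaemic results; it need not be a condition for reporting them.

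If a fuller protocol already provides for this, a sentence in the article's Outcomes section is enough.

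**Cost.** Two scripted questions on contacts already planned, one table and a short amendment; slightly longer calls and wide intervals. No change to the sample size. Trial status gives 20 May 2021 as the start of recruitment, so the report should state the date from which the prompts were used, because earlier follow-up would have only the general question.

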### Sample size calculation

Considering a type I error of 5%, a power of 90%, and the changes in FMD values as one of the primary outcomes [17], the sample size was computed to be 25 for each study group based on the two-sided t-test. To compensate for an approximate attrition rate of 20% throughout the research, we rise the final sample size to 30 adolescents in each group.

$$ n=\frac{{\left({Z}_{1-\alpha /2}+{Z}_{1-\beta}\right)}^2\times \left({S}_1^2+{S}_2^2\right)}{d^2} $$

(*α* = 5%, 1-β = 90%, *SD*_1_ = 2.7, *SD*_2_ = 2.7, *d* = 2.5)

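### Withdrawing randomised participants with under 80% compliance from follow-up restricts the primary FMD comparison to compliers and exposes it to a selection bias of unknown size

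*Protocol article*

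**What the plan says.** The rule stands at the end of the Study population section, after the eligibility criteria: those with "poor compliance (less than 80%) with the assigned intervention will be withdrawn from follow-up". It refers to an assigned intervention, so it applies after randomisation.

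The Intervention section says how compliance is measured: "Compliance will be evaluated based on unused supplements by each person", and "The remaining capsules will be counted to determine total supplement intake". Capsules are handed out monthly, over four visits from baseline to the end of the 12 weeks. The same section says that, for adverse events related to omega-3, "participants will be asked to stop taking supplements". Data management and monitoring adds that after a reported adverse event "more information is required to make decision about excluding the participants from the trial".

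The Methods part of the abstract says that FMD and the other clinical and laboratory assessments "will be done at the baseline and end of the trial". The Outcomes section defines the primary outcome as the "alteration in the value of FMD as an endothelial function marker at the end of the trial compared to the baseline value".

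The Sample size calculation gives 25 per group, raised to 30 with this reason: "To compensate for an approximate attrition rate of 20% throughout the research".

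**The concern.** Compliance is known only after assignment and can depend on it. A rule that ends follow-up on compliance lets a post-randomisation variable decide whose outcome is collected. Two routes could make the remaining groups differ:

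- **Prognosis.** Adolescents who skip capsules may also differ in how their diabetes is managed, and so in their FMD change.
- **Arm.** A participant told to stop capsules because of an omega-3-related event will have a low capsule count. The compliance rule then removes a person whose low count was caused by the treatment.

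FMD has a single post-baseline measurement, so a participant withdrawn at month 1 or 2 has no change score. An analysis plan can define populations, but it could at best impute a value that the protocol says not to collect. The attrition allowance replaces numbers and does nothing about who is missing. The same holds for every secondary outcome that needs an end-of-trial value.

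**Working it through.** **1. The plan's own figure.** Inputs from Sample size calculation: two-sided alpha 5%, power 90%, SD 2.7 in each arm, d = 2.5.

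n = (1.960 + 1.282)² × (2.7² + 2.7²) / 2.5² = 24.5, rounded up to 25 per arm. The stated 25 reproduces, and 25 × 1.2 = 30.

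**2. Loss of numbers alone.** If 20% are withdrawn in each arm, 30 × 0.8 = 24 remain. The standard error is 2.7 × √(2/24) = 0.779, and t-test power for 2.5 is 88.1% (89.4% by the normal formula). Numerical loss is largely covered by the allowance, so the issue is selection.

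**3. Selection when there is no treatment effect.** The document gives no compliance rate, no difference between arms and no link with outcome. These are assumptions, and a range is shown:

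- compliance is a normal trait with correlation r = 0.3 or 0.5 with FMD change;
- the least compliant fraction q of an arm is withdrawn;
- the SD stays at 2.7 and 30 are randomised per arm.

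The mean among those who remain shifts by r × 2.7 × k(q), with k(q) = φ(z_q)/(1 − q):

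- k(0.20) = 0.2800/0.80 = 0.350
- k(0.10) = 0.1755/0.90 = 0.195
- k(0) = 0

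The bias is the difference between the arms' shifts. The type I error is the rejection probability of the two-sided 5% t-test at that bias.

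| Withdrawn, omega-3 vs placebo | Remaining | Bias, r = 0.3 | Bias, r = 0.5 | Type I error |
|---|---|---|---|---|
| 20% vs 20% | 24 vs 24 | 0 | 0 | 5% |
| 20% vs 10% | 24 vs 27 | 0.3 × 2.7 × 0.155 = 0.13 | 0.5 × 2.7 × 0.155 = 0.21 | 5.3% to 5.8% |
| 10% vs 0% | 27 vs 30 | 0.3 × 2.7 × 0.195 = 0.16 | 0.5 × 2.7 × 0.195 = 0.26 | 5.5% to 6.5% |
| 20% vs 0% | 24 vs 30 | 0.3 × 2.7 × 0.350 = 0.28 | 0.5 × 2.7 × 0.350 = 0.47 | 6.6% to 9.6% |

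Against the planned 2.5, the last row is 0.28/2.5 = 11% to 0.47/2.5 = 19%, and the 20% vs 10% row is 5% to 8%. With better FMD change among compliers and more withdrawals on omega-3, the bias favours omega-3. If either is reversed, so is the sign.

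**4. The same question under another model.** Suppose instead that compliers and non-compliers differ by 0.5 to 1.0 SD in FMD change. The bias is then gap × 2.7 × (difference in withdrawal fractions):

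- 20% vs 20%: 0, type I error 5%.
- 25% vs 15%: 2.7 × 0.10 × (0.5 to 1.0) = 0.14 to 0.27, type I error 5.3% to 6.4%.
- 30% vs 10%: 2.7 × 0.20 × (0.5 to 1.0) = 0.27 to 0.54, type I error 6.4% to 10.6%.

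The order of magnitude is the same.

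**5. Price of following everyone.** All 30 per arm are analysed, with standard error 2.7 × √(2/30) = 0.697. Assume that non-compliers gain nothing:

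| Non-compliers | Expected difference | t-test power |
|---|---|---|
| none | 2.5 | 94.1% |
| 10% | 2.5 × 0.9 = 2.25 | 88.8% |
| 20% | 2.5 × 0.8 = 2.0 | 80.5% |

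With 20% non-compliers, the plan's own formula needs (1.960 + 1.282)² × 2 × 2.7² / 2.0² = 38.3, so 39 per arm, for 90% power.

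**The case against.** A reader might infer that the randomised comparison is lost, or that the FMD result will be biased. The documents do not support that. Bias under no effect needs unequal withdrawal, or a different selection mechanism, between arms. Nothing in the article gives a rate or an imbalance. Several features make imbalance less likely: double blinding, capsules matched in appearance, taste and smell, one capsule a day, and weekly calls. A difference in tolerability between omega-3 and glycerin capsules is conjecture. This stands, and it is why the range must include zero and why 20% versus 0% is a near-extreme case. It does not remove the risk, because stopping capsules after an omega-3-related event can still follow the arm.

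A reader might also infer that non-compliers' final FMD is certainly never measured. The article does not say when the 80% is judged. A total intake over 12 weeks is complete only at the last visit, when FMD is also due, and the value might then exist. Monthly dispensing makes earlier withdrawal just as possible. The timing is open, but both readings leave a comparison of compliers.

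Finally, the article names no as-randomised analysis set. That carries no weight here: a condensed article may leave it to a fuller document. The point rests on the withdrawal rule that the article does state.

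**Conclusion.** The concern holds as a risk of selection bias, not as a demonstrated one. Following the stated rule produces either avoidable missing primary outcomes or an exclusion of non-compliers from the analysis. Even with no bias under the null, the trial would estimate an effect in participants who took their capsules and not the effect of being assigned to omega-3.

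The size is unknown. Under the assumptions above it runs from nothing to just under a fifth of the planned difference, with the type I error between 5% and about 10%. The upper end needs all withdrawals in one arm and a correlation of 0.5. Lost numbers are a minor matter. The rule merits correction because outcomes that are not collected cannot be recovered at the analysis stage.

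The criticism concerns deliberate withdrawal for low compliance. Participants who no longer wish to take part may be unavoidable losses.

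**What to change.** - In Study population, delete poor compliance as a reason for withdrawal from follow-up.
- State that every randomised participant who still consents is invited to the planned 12-week assessment, whatever their capsule use and including those who have stopped capsules. This concerns data collection only and leaves the rules on stopping capsules as they are.
- In Statistical analysis, state that the primary comparison of FMD change is made by assigned group.
- Keep the 80% threshold only to define a per-protocol sensitivity analysis, labelled as such, and say when and from which capsule counts it is computed.

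**Cost.** The change is a short protocol amendment with no visits beyond those planned. The statistical cost is dilution, which should be stated openly and is more than slight: full follow-up of 30 per arm gives about 88.8% power with 10% non-compliers and 80.5% with 20%, against about 88.1% for a selected 24 per arm if the full 2.5 applies to them. The diluted figures assume that partial users gain nothing, which is the pessimistic end. If non-compliance near 20% is expected, the sponsor should either accept about 80% power or consider a larger sample, which is harder in a single-centre trial recruiting during the pandemic.
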